#### School absenteeism

School records of authorised and unauthorised half-day absences will be provided at the pupil level by school administration staff for participating pupils in the study for the academic years 2012–2013 (baseline) and 2013–2014 (12-month follow-up). These data are routinely collected by schools for all pupils as a legal requirement. Schools will provide the anonymised attendance data linked to the KiVa IDs to ensure that pupil anonymity is protected.

### Data collection

Table 1 summarises when the outcome data will be collected. Baseline data will be collected via pupil and teacher surveys in intervention and control schools in June/July 2013 for children in Years 2, 3, 4 and 5 (i.e., about to enter the Key Stage 2 Years 3, 4, 5, and 6). Data using the same measures will be collected at 12 months post-baseline (June/July 2014) for children coming to the end of Years 3, 4, 5, and 6.^3^Ethnicity, free school meals and SEN status (for baseline, or point of entry to school if the pupil joined the school subsequently) and absence data (for the academic years 2012–2013 and 2013–2014) will be collected by Autumn 2015.

**Table 1 Tab1:** Timing of data collection and intervention delivery

	June/July 2013	Sept 2013–July 2014	June/July 2014	By Autumn 2015
Intervention arm schools	Baseline outcome data collected for Years 2, 3, 4, 5	Delivery of KiVa programme	12-month post-baseline outcome data collected for Years 3, 4, 5, 6	Collection of school administrative data on ethnicity, free school meals, SEN status and absence.
Control arm schools	As above	Provision as usual	As above	As above

### Analysis of effectiveness of the KiVa intervention

The analysis will estimate differences at 12-month follow-up between the two trial arms, adjusting for baseline data. Statistical analyses will be reported in accordance with the CONSORT guidelines for cluster RCTs [49].

Baseline characteristics of the schools and pupils will be summarised separately for each trial arm using means and standard deviations (or medians and interquartile ranges) for continuous variables and numbers and percentages for categorical variables.

Comparison of outcomes at follow-up will be based on the intention-to-treat (ITT) principle with schools (clusters) and pupils analysed according to the trial arm they were allocated to, irrespective of the level of intervention actually received. The main reported findings will be based on analyses of 20 multiply imputed datasets generated (each using 10 cycles) using the fully conditional (“chained equations”) approach to “fill in” missing values [50, 51]. All study outcomes (primary and secondary), trial arm status, stratification and prognostic factors/confounders (outcome score at baseline, age, gender, ethnicity, qualifying for free school meals (child level) and special education needs (child level)) and potential effect modifiers of interest (see below) will be included in the imputation model.

Binary outcomes will be compared between trial arms using marginal logistic regression models using Generalised Estimating Equations with information sandwich (“robust”) estimates of standard error assuming an exchangeable correlation structure. Continuous outcomes will be compared using random effects linear regression. Both methods allow for correlation of outcomes within schools (clusters).

Tests of interaction will be performed to investigate whether the intervention effect on victimisation status at follow-up is moderated by victimisation status at baseline, gender and age, and whether the intervention effect on bullying status at follow-up is moderated by bullying status at baseline, gender and age. Tests of interaction will be considered to provide significant results if the p-value is less than 0.05. These analyses are purely exploratory, with any significant findings needing to be replicated in other studies to give them credence. Furthermore, we acknowledge the low power of these analyses.

The findings from analyses of imputed data will be contrasted with sensitivity analyses based on analysis of complete cases only (listwise deletion). The amount of missing data will be reported as a percentage for the main outcomes in each trial arm along with the amount of data recovered in the imputation analysis. The characteristics of children lost to follow-up will be compared to those retained in each trial arm to assess the nature of attrition.

Stata 13.1 will be used for the analyses using the *mi impute* and *mi estimate* commands to generate imputed datasets and analyse these, respectively.

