### Randomisation

As KiVa is a whole school intervention, the 20 schools (clusters) will be randomly allocated on a 1:1 basis to intervention and control conditions. Randomisation will be carried out by an independent registered trials unit at Bangor University (the North Wales Organisation for Randomised Trials (NWORTH)). Complete list randomisation using the dynamic adaptive algorithm^1^ [41] will be implemented, by a validated computer package with stratification by size of school (large/small split by the median) and proportion of children eligible for free school meals (high/low split by the median). Researchers are unable to remain blind to school allocation, as the implementation evaluation will be undertaken with schools when they are delivering the programme. However, the statisticians on the trial will be blind to allocation status. Schools will be informed of their assignment (intervention or control group) by Bangor University towards the end of May 2013.

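### The imputation model listed for the main findings does not name school, so followed as written it makes the primary standard error about 5-7% too small at the planned 10% missing follow-up

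*Protocol article*

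**What the plan says.** The point lies in the protocol article, under Analysis of effectiveness of the KiVa intervention. The headline analysis is fixed in some detail: "The main reported findings will be based on analyses of 20 multiply imputed datasets generated (each using 10 cycles"), by chained equations. The contents of the imputation model are then listed: "All study outcomes (primary and secondary), trial arm status, stratification and prognostic factors/confounders". The last group is spelled out as baseline outcome score, age, gender, ethnicity, free school meals and special educational needs. The list closes with "and potential effect modifiers of interest (see below) will be included in the imputation model".

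The list names neither school nor any product of arm and modifier, and nothing says that imputation is done by arm. Its only school-level items are the stratification factors, which the Randomisation section defines: "stratification by size of school (large/small split by the median) and proportion of children eligible for free school meals (high/low split by the median").

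Clustering is mentioned after the outcome models (GEE with robust standard errors, and random-effects regression): "Both methods allow for correlation of outcomes within schools (clusters"). The same section plans to test "whether the intervention effect on victimisation status at follow-up is moderated by victimisation status at baseline, gender and age", and does likewise for bullying. A complete-case analysis is the sensitivity analysis.

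**The concern.** The outcome models treat pupils in a school as correlated. An imputation model without school treats them as independent once arm, two binary splits and pupil covariates are known. Imputed pupils are then drawn around a mean shared across schools, which pulls the completed school means together. The robust standard error is built from the spread of those means, so it comes out too small. Rubin's between-imputation term does not restore the loss, because the imputation model carries no school-to-school variation.

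The error runs in the anti-conservative direction, on the primary result, in a trial with only 20 schools. The imputed analysis would also look more precise than the complete-case analysis for an artificial reason. The random-effects analyses of continuous outcomes share the mismatch in principle; its size was not computed for them.

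A secondary concern is moderation. If the imputed values carry no arm-by-modifier product, estimated interactions are drawn toward zero.

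**Working it through.** **Inputs from the article.** Sample size section: 10 schools per arm, 125 eligible pupils per school, 95% consent, 10% drop-out, ICC 0.025, 16% against 8%, two-sided 5%. Recruitment and retention section: leavers and absentees at follow-up are not expected to exceed 10%.

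**The plan's own figure.**
- Pupils per school: 125 × 0.95 = 118.75 consented; × 0.90 = 106.9 followed up.
- Design effect: 1 + (106.875 − 1) × 0.025 = 3.647. Effective n per arm: 1068.75 / 3.647 = 293.1.
- Continuity-corrected two-proportion test: z = [0.08 − 1/293.1 − 1.96 × √(2 × 0.12 × 0.88 / 293.1)] / √[(0.16 × 0.84 + 0.08 × 0.92) / 293.1] = (0.0766 − 0.0526) / 0.0266 = 0.90, so power is 81.6%. This reproduces the stated figure, so the inputs are read as the plan uses them.

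**Algebra with school omitted** (arm-only imputation model, missing completely at random). Let m be the missing share, 0.10. Variances are per school, with total outcome variance set to 1.
- True variance of a school mean: 0.025 + 0.975 / 106.9 = 0.0341.
- Between-school variance in the completed data: (1 − m)² × 0.0341 + m² / 11.9 = 0.0276 + 0.0008, where 11.9 is the number of imputed pupils per school.
- Between-imputation term: (1 + 1/20) × (m² / 11.9 + m² / 106.9) = 1.05 × 0.0009 = 0.0010.
- Rubin total: 0.0276 + 0.0008 + 0.0010 = 0.0295 (from unrounded terms).
- SE ratio: √(0.0295 / 0.0341) = 0.93.
- Actual two-sided level of a nominal 5% test: 2 × [1 − Φ(1.96 × 0.93)] ≈ 6.9%.
- ICC in the imputed data: about 0.81 × 0.025 = 0.020.

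At other missing shares, which are assumptions, the same formula gives SE ratios of 0.96 at 5%, 0.90 at 15% and 0.87 at 20%.

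**Simulation closer to the listed model.** 500 null trials, 20 schools of 119 pupils, 10% of outcomes missing completely at random, 20 imputations, exchangeable GEE with robust SE. The imputation model held arm, baseline outcome and two strata; the baseline coefficient was assumed (log-odds 1.2).

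| Analysis | Mean SE | Mean SE / empirical SD | Rejection, nominal 5% |
|---|---|---|---|
| Complete cases | 0.212 | 0.97 | 8.4% |
| Imputed, school omitted | 0.201 | 0.92 | 9.0% |
| Imputed, school included | 0.219 | 1.00 | 7.6% |

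Omitting school gives an SE about 5% below complete cases (0.201 / 0.212 = 0.95). Monte Carlo error on the SE ratios is about 0.03, but the methods were compared on the same datasets. A larger run (3000 null trials, arm-only imputation) gave an imputed-to-complete-case SE ratio of 0.933. Rejection rose from 8.2% to 9.8% with z tests, and from 5.3% to 6.6% with a small-sample correction.

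**Interaction (secondary).** With an assumed true log-odds interaction of −0.7 and 10% missing (250 replicates), main-effects imputation averaged −0.588, against −0.655 with the product in the imputation model and −0.658 for complete cases. Since 0.588 / 0.655 = 0.90, the attenuation is about 10%. Power fell from about 0.60 (complete cases) to 0.52.

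**The case against.** The strongest reply is that this is a condensed article whose analysis plan is not shown. It says which variables will be included, not that the list is complete, and it never says school is left out. That is right as far as it goes. A reader might infer that the plan excludes school, or that it enters modifiers as main effects only; neither is stated. Indeed all three modifiers already stand among the prognostic factors, so the closing clause about modifiers is either redundant or concerns how they enter, and the text does not settle which. What remains is that the article fixes the number of datasets, the cycles, the variables and the software commands. An analyst who follows that list would impute without school, which makes this more than an omitted detail.

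Second, the size is modest, and neither check ran the full listed model. Teacher ratings, absence records and other covariates might absorb some of the school effect. In the simulation, baseline outcome and the strata did not remove the understatement, but the exact size under the full model is unknown.

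Third, the planned complete-case contrast does not share the flaw, so a reader could see an artificial gain in precision. It would not correct the result reported as the main finding.

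Fourth, the moderation tests are declared to be of limited standing: "These analyses are purely exploratory, with any significant findings needing to be replicated in other studies to give them credence", and the article concedes their low power. That limits the interaction point to a secondary remark.

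**Conclusion.** The concern holds in a limited form and is a should-fix. Followed as written, the listed imputation model ignores the school effect. At ICC 0.025 and 10% missing follow-up, the primary SE is about 5-7% too small: about 7% by algebra with an arm-only model, and about 5% relative to complete cases in the simulation with baseline outcome and strata. That adds roughly 1 to 2 percentage points to the type I error: 1.9 by algebra, 1.3 to 1.6 in the larger run. In the smaller run it was 0.6 against complete cases and 1.4 against imputation with school.

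These figures assume data missing completely at random. The effect grows if more than 10% is missing (SE ratio about 0.90 at 15%), but the article does not expect more, so larger shares are assumptions.

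A reader might take rejection rates of 9% or more as the damage done by imputation. They are not: complete cases already reject at about 8%, because robust standard errors are being used with 20 schools and a normal reference. That is a separate matter.

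The interaction attenuation of about 10% at 10% missing applies only if modifiers enter as main effects, as the list reads but does not say.

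**What to change.** State that the chained equations are run separately in each arm, with school included in every imputation equation as indicators. The two stratification splits are constant within a school, so the indicators absorb them and they should be dropped from those equations. Imputing by arm also preserves the planned arm-by-modifier interactions without product terms.

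Rare binary outcomes need a stated fallback. At the pilot's 2% bullying rate after the programme, a school with 107 observed pupils has about a 12% chance of no events (0.98^107 = 0.115), so about one of 10 intervention schools could give perfect prediction. Use augmented regression or a school random intercept there, after confirming that the chosen option can be run alongside the named Stata commands.

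The cost is some extra imputation coding and a slightly conservative SE: about 3% above complete cases at 10% missing (0.219 / 0.212 = 1.03; 1.026 in the larger run). No new data or design change is needed.

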### Process evaluation

#### Implementation fidelity

The objective of the first part of the process evaluation is to describe the level of implementation fidelity as assessed by the teacher-completed online Teacher Lesson Record Books (for class lessons) and independent observations (for the school-wide element). Data on the fidelity of programme implementation will be collected for intervention arm schools and waitlist control schools when they subsequently deliver the intervention. Although the analyses of effectiveness are based on data collected during the trial period only, the process evaluation will use data from the waitlist controls as well.

Quantitative data relating to the delivery of the KiVa lessons will be collected using KiVa online teacher lesson record books. The teachers document the following: time spent preparing each lesson; time spent delivering each lesson; which parts of the lesson were delivered; their view on the suitability of lesson content; and the proportion of pupils who were positively engaged in the lesson. In line with previous research on the fidelity of delivering KiVa lessons [52], the analysis will focus on adherence (to lesson content), exposure (length of lessons) and quality (using time spent preparing lessons as a proxy). Lesson adherence will be calculated as the proportion of tasks delivered for each lesson averaged over the 10 lessons (expressed as a percentage). Lesson duration will be calculated as the number of minutes used for teaching lesson content averaged across the lessons a teacher is reported to have delivered. Time spent preparing the lessons will be calculated by averaging the reported number of minutes across the lessons delivered by a teacher.

School-wide programme implementation will be assessed by independent observation (one per school, conducted in Spring 2014 for intervention schools and Spring 2015 for control schools). These school observations will be undertaken to look at how the schools are delivering the programme and examine differences and similarities in delivery across different school contexts. School-wide observations will use a list of eight items and researchers will score each one on a three-point scale (0 = “not true”, 1 = “somewhat true”, 2 = “certainly true”) with additional space for recording notes to support the score given. Items cover: the visibility of KiVa materials in the school; the extent to which the headteacher, playtime supervisors, a Key Stage 2 teacher (or the KiVa team lead) and Key Stage 2 pupils can talk fluently and knowledgably about the programme; evidence of a KiVa team logbook being used to record incidents of bullying and how they were dealt with; and whether parents know what the programme is, have received information about it from the school and have used the website (schools will select parents, and it is acknowledged that they will be unrepresentative). Scores on the school observation measure will be summed to give an overall score for each school in the range 0 to 16, where a higher score indicates stronger school-wide implementation. These scores and the observers’ comments will be used to help identify common strengths and weaknesses as regards implementation. Again, analyses will use data on KiVa delivery in intervention and waitlist control schools.

#### Scale issues

The second part of the process evaluation will explore issues relating to potentially scaling up KiVa in Wales using focus groups and structured interviews. The focus groups will be held with key stakeholders in the implementation of school-based bullying interventions, namely policy makers/anti-bullying advocates (including Welsh Government, local education authorities, anti-bullying NGOs, teacher unions), teachers and other educators (working in KiVa schools), and parents/children (also from KiVa schools). They will consist of facilitated discussion, supported by a series of questions and prompts, of three main topic areas relevant to the scalability of KiVa in Wales: the need and demand in Wales for anti-bullying programmes generally and KiVa specifically, and how to build demand; how well KiVa fits with the social, political and cultural context in Wales and with the educational context (including the curriculum); and, should the trial results be positive, how the implementation of KiVa at scale in Wales can best be enabled and supported given the context (to cover the most suitable support structure for implementation, including training, technical assistance and financing). It is planned to hold 18 focus groups, or as many as needed for data saturation (i.e., fewer may be sufficient). Focus group data will be analysed using thematic analysis [53] to identify themes relevant to developing a scalable model of the programme. Data will be coded deductively, focusing on data items related to need/demand, attitudes towards the KiVa programme, and sustainability.

The structured interviews will be conducted with headteachers in schools delivering KiVa and teachers who deliver the programme, and will elicit their experiences of implementing KiVa. The interview content will cover the following: how the programme is working in the school; what teachers like or dislike; any observed benefits for the school; any challenges of implementation (and efforts to overcome those challenges); and any reflections on how implementation may better be supported in Wales. A narrative summary of the structured interviews with teachers will be produced.

### Micro-costing

The study will estimate the cost per school and per child of setting up and implementing the KiVa programme in Wales. A micro-costing analysis will be undertaken to determine the cost of implementing KiVa in the intervention arm schools in the first year (i.e., during the trial), including set-up or non-recurrent unit costs (e.g., purchasing materials, training staff) and recurrent unit costs (e.g., staff time, yearly registration costs) for the programme. Costs related to undertaking the research evaluation will be excluded where they are not integral to the implementation of the KiVa programme. Micro-costing is a bottom-up approach used to estimate the cost of setting up and delivering an intervention. It involves collecting detailed information about the resources required to deliver an intervention, and subsequently assigning economic unit costs to each component of resource use. The alternative approach would be gross-costing, a top-down approach where the total cost invoiced is divided by the total resource use to obtain an average cost of resource use. The micro-costing approach is accepted as being more accurate than gross-costing, and is widely used in costing studies [54–56].

Costs will be presented in UK Pounds Sterling for the financial year 2013–2014. Structured forms (record books) will be developed and distributed to the designated KiVa lead at participating schools, together with the KiVa project team (responsible for providing materials, training, supervision and additional support). These record books will ascertain how much time the KiVa lead and other school staff spend each month on activities directly related to implementing KiVa (e.g., staff meetings, setting up and inviting parents to a meeting to introduce the programme). The fidelity measures will also be used to assess the amount of time teachers spend on lesson preparation and delivery. Additionally, the KiVa lead for the school will be asked to complete a structured form summarising how much time school staff spend travelling to training and supervision sessions. Time spent by teachers and other school staff at supervision sessions will be calculated using attendance records completed by the KiVa project team. The KiVa project team will also be asked to provide details summarising costs and time related to providing materials, training, supervision and additional support.

For the analysis, teacher costs will be based on data collected regarding staff time multiplied by national average salaries for a mid-point M5 qualified teacher. A school year of 38 weeks for the delivery of KiVa will be assumed, taking sickness, Continuing Professional Development and holidays into account. Salary calculations will be inclusive of employers’ on-costs (25 %). The KiVa programme costs will be separated into recurrent and non-recurrent costs and will exclude costs related to undertaking the evaluation. The various elements will be summed and divided by the number of schools (i.e., 10) delivering KiVa in the trial to give an average cost per school. In order to calculate the average cost per child, the total cost will be divided by the number of children receiving the intervention.

### Ethical approval

Ethical approval was granted by the School of Psychology, Ethical and Governance Board, at Bangor University on 30^th^ May 2013 (Ethical approval code: 2013–9162).

